## Methods/Design

### Aim of the study

We will perform an RCT involving whole body vibration exercise in patients with chronic low back pain in order to determine:

1) whether WBV exercise is effective for the treatment of chronic LBP,

2) whether WBV exercise produces more beneficial effects than general exercise for chronic LBP, and

3) adverse effects associated with whole body vibration.

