### Study design

This is a single-blind randomized controlled trial comparing a WBV exercise with general exercise (Figure 1). A total of 120 patients with chronic LBP will be recruited and investigated from Shanghai Shangti Orthopedic Hospital and Shanghai University of Sport, Shanghai City, China.

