**Figure 1 F1:**
[figure not shown]
Flow diagram showing whole body vibration exercise for patients with low back pain (LBP).

All participants, prior to initiation of the study, will accept a questionnaire asking for the following details: basic information (for example, age), past and present job status, medical history, pain (visual analog scale, VAS), back function (Oswestry Disability Index, ODI) and exercise habits (for example, frequency and time/session). Prior to inclusion, informed consent will be sought from all participants in the study.

The subjects will be allocated in a 1:1 ratio by computer-generated randomization if they meet the inclusion criteria. After randomization, patients with chronic LBP will be assigned to the control group (general exercise) or to the intervention group (WBV exercise). The total study period will be 6 months, which has a 3-month intervention and 3-month follow-up period with no intervention. The study will include assessments at the following time points: before intervention, at 3 months, and at 6 months.

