### Statistical analysis

The SPSS 17.0 and Microsoft Excel 2007 software will be used to perform statistical analyses. Data will be expressed as mean?±?standard deviation (SD). We will use two-way repeated measures analysis of variance (group?×?time) to compare the effect of WBV exercise group with the control group, including the primary and secondary outcomes. If subjects are lost to follow-up, an intention-to-treat analysis will be conducted. A T-test will be used to compare the changes in measures within groups when the analysis of variance reveals a significant difference. Statistical significance is a *P* less than 0.05.

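### The only follow-up test prescribed after the group-by-time ANOVA is a within-group t-test, and the interaction is not named as the test of vibration or as the gate

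*Protocol article*

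**What the plan says.** All of the analysis text is in the Statistical analysis section of the protocol article.

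- Main method: "We will use two-way repeated measures analysis of variance", with group and time as factors. Its stated purpose is "to compare the effect of WBV exercise group with the control group, including the primary and secondary outcomes".
- Follow-up: "A T-test will be used to compare the changes in measures within groups when the analysis of variance reveals a significant difference".
- Significance level: P "less than 0.05".

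The second item under Aim of the study asks "whether WBV exercise produces more beneficial effects than general exercise for chronic LBP", which is a question about the difference between arms. The first item there asks whether WBV is effective and names no comparator.

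Under Study design, the visits are "before intervention, at 3 months, and at 6 months". Under Control group, the comparator does the identical exercises with the vibration left out. Strengths and limitations presents that matching as an advantage of the design.

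**The concern.** A two-way repeated measures ANOVA gives three results: group, time, and group by time. Only the interaction asks whether the arms change differently. The time effect pools both arms. The group effect averages over all visits, including the one before treatment. The article does not say which of the three counts as the significant difference that opens the t-tests.

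Both arms exercise, and the Participants section requires pain of more than 3 months at entry. Improvement over time in both arms is therefore plausible even if vibration does nothing. If the time effect opens the gate, the plan leads to a before-after test in each arm. A significant change in the WBV arm, or in that arm but not in the control arm, could then be reported as a vibration effect. The aim without a comparator makes that easier. Such a test also gives up what the matched control was designed to provide.

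The follow-up is the wrong kind even when the interaction is significant. Two within-arm tests give neither the size of the difference between arms nor the visit at which it arises.

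**Working it through.** **Inputs from the article.** "A total of 120 patients with chronic LBP will be recruited" and "The subjects will be allocated in a 1:1 ratio by computer-generated randomization", so 120 / 2 = 60 per arm. There are three visits and alpha is 0.05.

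**Assumptions.** The article gives no SD, correlation, effect size or power, so there is no stated figure to reproduce. I assumed SD 1 at each visit, equal correlation between visits of 0.5 or 0.7, two-sided tests and no dropout. Both arms improve by the same amount *d* (in SD units) at 3 and 6 months, so there is no true arm difference.

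**Check.** 5,000 simulated trials per setting, with mixed two-way ANOVA F-tests at 0.05, followed by a t-test of the baseline-to-3-month change in each arm. Each pair of figures is for correlation 0.5 / 0.7, in % of trials. *WBV only* means that the WBV arm improves significantly and the control arm does not.

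| *d* in both arms | Any ANOVA effect significant | Any-effect gate: WBV significant | Any-effect gate: WBV only | Interaction gate: WBV only |
|---|---|---|---|---|
| 0 | 15.3 / 14.5 | 1.5 / 1.1 | 1.5 / 1.0 | 0.7 / 0.5 |
| 0.2 | 64.3 / 85.0 | 30.0 / 49.1 | 18.7 / 23.4 | 1.9 / 2.0 |
| 0.3 | 94.1 / 99.5 | 62.6 / 84.2 | 21.7 / 13.2 | 1.9 / 1.4 |
| 0.5 | 100 / 100 | 96.3 / 99.9 | 2.4 / 0.2 | 0.5 / 0.1 |
| 0.8 | 100 / 100 | 100 / 100 | 0 / 0 | 0 / 0 |

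Across all settings the interaction test was positive in 4.6% to 5.5% of trials, and a between-arm t-test on change in 4.7% to 5.8%. Both are close to the nominal 5%.

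**Analytic check.** The SD of a change is √(2(1 − ρ)), which is 1 at ρ = 0.5. The noncentrality of the within-arm t-test is *d*√60 / SD of change.

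- *d* = 0.3, ρ = 0.5: 0.3 × 7.746 = 2.32, so power *p* = 0.628. Without a gate, WBV only = *p*(1 − *p*) = 0.628 × 0.372 = 0.234. The gate opens in 94% of trials, which brings it to the simulated 21.7%.
- *d* = 0.5, ρ = 0.5: 0.5 × 7.746 = 3.87, so *p* = 0.968. The gate is always open, so WBV only = 0.968 × 0.032 = 0.031. The simulated 2.4% is somewhat low. A repeat with 40,000 trials gave 3.0%, so about 3% is the better figure for that cell.

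Since *p*(1 − *p*) peaks at *p* = 0.5, the WBV-only pattern is most frequent at modest improvement and disappears at large improvement. At large improvement the WBV test is almost always significant by itself, still with no vibration effect.

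**The case against.** The strongest reply is that the article does plan a between-arm test. The ANOVA comes first, covers primary and secondary outcomes, and has comparison of the arms as its stated purpose. Its interaction is valid and holds its level. A reader might infer from the t-test sentence that a vibration effect could be claimed with no test between arms at all. The Statistical analysis section does not support that.

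A reader might also take it as settled that a time effect is enough to start the t-tests. The sentence does not say so. Because it follows a statement about comparing the groups, a difference between groups is at least as natural a reading. On that reading the WBV-only pattern is held to about 2%. A false claim would also require the authors to pass over their own non-significant interaction.

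The rates depend on the assumptions. It would be tempting to quote how often the two arms disagree on significance: without a gate, 2 × 0.628 × 0.372 = 47% at 0.3 SD and correlation 0.5. Half of that is control-only, which cannot produce a false claim for WBV.

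Finally, a separate analysis plan may define contrasts at 3 and 6 months, and their absence from an article is not in itself a fault. This stands too. It does not remove the point, because the article does more than omit detail: it prescribes a follow-up test, and that test does not address the comparative aim.

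**Conclusion.** The concern holds in a limited form. The ANOVA contains a valid between-arm test, but the article does not name the interaction as the test of vibration or as the gate. The one follow-up it prescribes is within groups and cannot answer the comparative aim.

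Under the assumptions above, the any-effect reading gives a WBV-only result in about 13% to 23% of null trials at 0.2 to 0.3 SD improvement in both arms, and in about 3% or fewer at 0.5 SD. The interaction gate holds it to about 2% at most. These rates illustrate one reading of an unclear sentence and are not predictions for this trial. That the follow-up cannot show when or by how much the arms differ depends on none of them.

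**What to change.** Replace the t-test sentence with wording to this effect: *The group-by-time interaction is the test of the vibration effect and the only result that opens follow-up testing. Follow-up consists of the between-arm difference (WBV minus control) at 3 months and at 6 months, adjusted for the baseline value, each with a 95% confidence interval. Within-group changes are reported descriptively and are not tested.*

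If a separate analysis plan exists, bring it into line. Trial status reports that recruitment is underway, so the change should be dated and made before outcome data are analysed. The cost is a small amount of analysis work. Baseline, 3-month and 6-month values are already scheduled, so no new data are needed.

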## Discussion

Based on the theory of WBV, it should be an effective treatment for chronic LBP. However, the evidence of WBV is inadequate, and the effect of WBV exercise is disputed for LBP. We will perform a prospective, single-blind, randomized controlled trial of WBV exercise for patients with chronic LBP. We think the study could bring about the proof that WBV may offer an alternative treatment for chronic LBP. WBV exercise could produce more beneficial effects than general exercise for chronic LBP, by reducing pain and improving function and quality of life.

### Strengths and limitations

First, most previous WBV exercise studies have typically ranged in duration from a few weeks to 3 months [20,21,23,24]. The study duration is an intervention period of 3 months and a follow-up period (with no active intervention) of 3 months, giving a total study period of 6 months. Second, in our study, intervention group performs five movements with vibration, but the control group receives the five same movements without vibration for an equal amount of time. Based on this point, the study could reduce other bias compared to previous studies [20-25]. Third, previous studies have mainly focused on pain, back disability, and quality of life. But trunk proprioception and transversus abdominis activation capacity are rarely analysed for WBV exercise on chronic LBP. There are also some limitations in our trial. The total number of subjects involved in the study is not large (120 patients). Moreover, only one vibration frequency (18 Hz) is used to estimate the effect of WBV for chronic LBP; different vibration frequency groups should be added to subsequent studies.

In conclusion, this study aims to determine the effect of WBV exercise for chronic LBP, and to estimate whether WBV exercise produces more beneficial effects than general exercise for chronic LBP. The results of the study will be of benefit to patients, researchers and policy makers with an interest in treatment of LBP.

## Trial status

Patient recruitment is underway.

## Abbreviations

LBP: low back pain; ODI: Oswestry disability index; PBU: pressure biofeedback unit; RCT: randomized controlled trial; SD: standard deviation; SF-36: short form 36; VAS: visual analog scales; WBV: whole body vibration.
